## Abstract

**Background:**

People with disadvantaged backgrounds are less likely to visit the dentist for planned care, even though they have disproportionately poorer oral health. They are correspondingly more likely to experience dental problems and use urgent dental care, general practices and Accident and Emergency departments, which not only makes meeting their needs expensive, but, since these services often rely on prescriptions rather than addressing the clinical cause, can contribute to antimicrobial resistance.

**Methods:**

The RETURN intervention has been developed with substantial community co-production, to be delivered opportunistically in urgent dental care settings. This brief intervention is delivered by dental nurses and involves material relevant to the ‘in-group’ targeted. The material includes booklets relating to barriers to planned dental visiting with corresponding short video clips featuring local people and including a modelling element. Dental nurses are trained to have supportive and non-judgemental conversations, assisting patients to set personal goals and action plans, which are reinforced in a follow-up text within a few weeks. A randomised controlled trial will be undertaken in 3 types of sites: dental practices delivering urgent care (a) within working hours, (b) out of hours, and (c) in a Dental Hospital. The trial will recruit 1180 adult urgent dental care users over 12 months, who have not visited a dentist for a planned care appointment for 2 years or more and do not have a dentist who they visit for routine care. It aims to investigate the effectiveness and cost-effectiveness of the intervention and to explore whether the intervention has different effects across the socio-economic gradient. Participants will be followed up at 6, 12 and 18 months after randomisation. Co-primary outcomes are attendance at a dental practice for planned care within 12 months and self-reported oral health-related quality of life at 12 months.

**Discussion:**

This is a pragmatic trial, evaluating the effectiveness of the intervention under the usual condition in which it might be applied. Since dental practices work as independent contractors to the NHS, this brings implementation and fidelity challenges which will be explored and described in embedded qualitative work.

**Trial registration:**

ISRCTN registry identifier ISRCTN84666712. Registered 12/04/2021.

## Administrative information

Note: the numbers in curly brackets in this protocol refer to SPIRIT checklist item numbers. The order of the items has been modified to group similar items (see http://www.equator-network.org/reporting-guidelines/spirit-2013-statement-defining-standard-protocol-items-for-clinical-trials/).

## Introduction

### Background and rationale {6a}

Dental diseases are both very common and expensive to treat, with costs amounting to an estimated $356.80 billion in treatment expenditures and $187.61 billion in productivity losses worldwide [1]. Unfortunately, an inverse care law exists whereby those who have the highest dental needs are the least likely to receive good quality care—a pattern which is both considerable and globally consistent [2, 3]. A social patterning of dental attendance exists where those from more deprived socio-economic backgrounds are less likely to visit a dentist for planned visits [3–5], even though poorer oral health disproportionately affects those at the lower end of the socio-economic spectrum [6–8]. Several studies have shown that socio-economic inequalities in oral health are, at least some extent, mediated by dental attendance [9–11]. A large body of evidence, including longitudinal studies, show that dental attendance is linked to better oral health [4, 12, 13]. Patients who are regular dental attenders are also more likely to report fewer negative impacts of poor oral health on their quality of life [5].

As many as a third of the UK population report that they only attend a dentist when they have a problem, or never do [14]. While early studies tend to adopt a dichotomous distinction between regular and irregular attenders [6], often based on dental attendance over the preceding 12 months, more recent studies have started to look at patterns in dental attendance in terms of the lifecourse [5, 15–17]. These studies show that only a minority of patients maintain dental attendance patterns consistently throughout their lives, and a small minority never visit a dentist. Consistent planned dental visits over the long term have been shown to be associated with better oral health, compared to patients who do not visit a dentist at present, but used to do so, or patients who have never regularly attended dental care services [5, 15, 17].

Planned care refers to services for pre-arranged appointments as opposed to urgent care appointments. Planned care appointments are arranged relating to either an examination or check-up or a course of treatment (where further care is identified as needed following an examination). Regular check-ups are recommended so that an early diagnosis of oral disease can be made (dental caries, periodontal disease, oral cancer). These check-ups also allow for the detection of the oral manifestations of systemic disease and appropriate referral and establishing a therapeutic alliance (relationship) between the provider and patient which helps support patients’ adherence to preventive recommendations [18]. As well as monitoring patients’ oral health and allowing secondary prevention (limiting progression and effect of oral diseases at an early a stage, by, for example applying fluoride varnish to early demineralised lesions), check-up visits often incorporate a third role in primary prevention—influencing patient behaviour with a view to preventing oral diseases before they occur, where members of the dental team give advice to help patients improve their tooth-brushing and dietary behaviours and stop smoking [18].

What constitutes ‘regular’ visits in terms of the optimal frequency for visiting a dentist for a check-up has been the topic of considerable debate, with recommendations varying from 6-monthly examinations (recall visits) to longer periods tailored to the level of patients’ risk of developing problems (usually up to 2 years for people with low risk of disease) [18, 19]. Since there is general agreement that planned dental visits at least every 2 years are beneficial for monitoring purposes with prevention and treatment as needed; we define planned dental visiting behaviour as having visited a dentist in the past 24 months for a non-urgent appointment.

People with irregular attendance patterns often tend to be those who wait until there is a problem such as toothache and swelling which impacts their quality of life [20]. More than 25% of UK adults report they had dental pain over the last 12 months, and this is disproportionally affects people with manual backgrounds [21]. Patients attending for a dental emergency have often been in pain for over 2 weeks, and a significant proportion of those attending dental emergency services, do so repeatedly for the same condition [22]. Some people, even when in pain, avoid using dental services and visit other services such as General Practice (GP) or Accident and Emergency (A&E) departments instead, which increases the costs of meeting their dental needs and puts an added burden on these often stretched services [23].

Since General Practitioners (GPs) prescribe antibiotics for over half of patients who attend their services with dental problems, this, together with the high level of antibiotics prescribed in dental practice for people attending with urgent problems, contributes to the problem of antimicrobial resistance [24–27]. In addition, there are potentially serious consequences if dental infections remain untreated, such as sepsis, which may require hospitalisation, resulting in high costs to the National Health Service (NHS) [28]. In short, a lack of planned dental visiting can result in dental visits for acute dental problems which is expensive and of limited effectiveness—geared towards giving only short-term relief of symptoms [29].

A brief psychological intervention (the RETURN intervention) has been developed to be delivered to adults attending dental services for urgent care which aims to promote planned dental visiting. The intervention has been developed using extensive qualitative work [16] and with patient and public involvement to identify salient barriers to planned dental care. This work also helped to develop appropriate imagery and narrative for the intervention material, including video stories from local people which accord with the ‘in group’ identity of the population targeted. This is in recognition of identity-based motivation theory which explains that people are most likely to be motivated and act towards goals if they see that the action is in congruence with their perceived self-identity [30].

In order to promote planned dental visiting, and through this to improve oral health, and reduce impacts of oral disease such as toothache and use of antibiotics for dental problems [29], the intervention uses multiple behaviour change techniques. The intervention is delivered by dental nurses who have been trained to discuss the intervention material with patients using active listening techniques such as relevant open questions, non-judgemental language, non-directive talk and acknowledging patient’s priorities, beliefs and challenges. The intervention is aimed at helping patients overcome their barriers to dental attendance for planned care and includes a ‘goal setting and action plan’ element [31]. Goal setting (a distal goal, e.g. attending for planned dental care) and creating an action plan to achieve it may help patients overcome significant barriers preventing behaviour change. Action planning involves proximal goals; in this case, these smaller achievable short-term goals would be designed to overcome a patient’s specific barrier(s). These techniques are simple to administer and are known to assist people with achieving health-related behaviour change [32]. The delivery of the RETURN intervention has been previously tested in a feasibility study. There are no known risks of the intervention, to either the trial participants, or the trial research teams, although there is a possibility that participants experience a heightened dental anxiety after thinking in detail about visiting a dentist. Possible benefits of the intervention are improved oral health and quality of life after taking up planned dental care, with avoidance of dental emergencies and its impact on the cost to the NHS.

### Objectives {7}

The overall objective of this trial is to assess the effectiveness and cost-effectiveness of the RETURN intervention for urgent dental care service users and to explore whether the RETURN intervention has different effects across the socio-economic gradient.

#### Primary objectives

To identify whether there is a difference between intervention and control groups in rates of attendance for a planned care appointment at a dental practice within 12 months (as measured by NHS Business Services Authority [BSA] data).To identify whether there is a difference in oral health-related quality of life 12 months after randomisation.

#### Secondary objectives

To identify whether the behavioural intervention has different effects across the socio-economic gradient.To identify the psychological factors which mediate any intervention effect.To identify whether there is a difference between intervention and control groups in self-reported rates of attendance and/or attempts to make an appointment at a dental practice for planned dental care during the follow-up period.To identify whether there is a difference between intervention and control groups in rates of attendance at a dental practice (as measured by BSA data) for a planned care appointment within 18 months.To identify whether there is a difference between intervention and control groups in oral health quality of life at 6 and 18 months.To identify whether there is a difference between intervention and control groups in halitosis and bad taste as indicators of dental infection at 6, 12 and 18 months.To identify whether there is a difference between intervention and control groups in clinical dental treatment received at 6, 12 and 18 months.To identify whether there is a difference between intervention and control groups in self-reported rates of attendance for urgent dental care at A&E, GP practices and urgent dental care services at 6, 12 and 18 months.To identify whether there is a difference between intervention and control groups in rates of antibiotics or analgesics for dental problems prescribed by a dentist, GP Accident and Emergency department or walk-in centre at 6, 12 and 18 months.To monitor any change in dental anxiety after receiving the intervention.To estimate the cost effectiveness of the intervention compared with usual care at 12 and 18 months.

### Trial design {8}

The RETURN trial is a randomised, open-label, superiority study involving delivery of an opportunistic psychological intervention to urgent dental care users developed to increase the uptake of planned dental care and reduce health inequalities. The allocation ratio between intervention and control is 1:1. The trial will recruit 1180 urgent dental care users over 12 months. Participants will be followed up at 6, 12 and 18 months after randomisation.

## Methods: participants, intervention and outcomes

### Study setting {9}

Recruitment will be in three site types: a teaching Dental Hospital (Liverpool University Hospitals NHS Foundation Trust); NHS dental practices providing care out-of-hours; and NHS dental practices providing in-hours urgent care, all located in Cheshire and Merseyside which is in the North West of England, UK. A list of sites can be obtained from the research team.

### Eligibility criteria {10}

#### Inclusion criteria

Patients eligible for the trial must comply with all of the following at randomisation:Adults (aged 18 years or over) seeking urgent dental care.Has not visited an NHS or Private dentist for a non-emergency appointment (i.e. when not in pain or symptomatic) for 2 years or more, and do not have a dentist who they visit regularly for routine care.Able to provide either a telephone number, email or postal address to allow follow-up.Has provided written consent.Has adequate understanding of spoken and written English.Are responsible for making their own dental appointments, i.e. not done by a carer.

#### Exclusion criteria

Any patient meeting any of the criteria listed below at baseline will be excluded from trial participation:Have previously been enrolled in the RETURN feasibility or main trial.Lives with, or related to, a participant in the RETURN feasibility or main trial.

Patients who go on to have planned care with undergraduate students in the Dental Hospital will not be excluded, although the route that patients’ take to planned care will be reported.

### Who will take informed consent? {26a}

Following screening, consent will be sought from potentially eligible patients by RETURN trained staff, who are delegated and qualified to do so. This includes dental nurses in urgent care services who have received training in taking this consent and are observed to reach competency in this by a member of the research team.

### Additional consent provisions for collection and use of participant data and biological specimens {26b}

Participants will be given the option in the consent form, to opt into or out of consenting to their data potentially being used in future studies. No biological specimens are being collected in this study.

### Intervention

#### Explanation for the choice of comparators {6b}

Participants will receive the usual care that is provided by the site they were recruited at.

#### Intervention description {11a}

Participants randomised to the RETURN intervention will receive a booklet pack providing educational resources to help overcome six common dental visiting barriers (‘I don’t have time’, ‘I don’t think to go when I’m not in pain,’ ‘I don’t have trust in dentists’, Cost, Embarrassment, Anxiety). The booklet pack contains a set of resources to help participants prepare for and support their attendance for a planned dental appointment, such as information on the cost of treatment and how to claim for free care if in an exempt from charges group; relaxation exercises which they might use when waiting for their dental appointment, and a credit card sized information card, which the participant can give to their employer advising that further dental care appointments are recommended. The pack contains some persuasive communication material, such as information about the consequences and costs of delaying care until they have toothache. A leaflet describing how dental services operate during the COVID pandemic will also be included, including for example having to wait outside the practice until just before their dental appointment time.

A trained dental nurse or research dental nurse (trained dental nurses employed by the research team) will help the participant identify a barrier which is most important to them using behaviour change conversational techniques such as empathic listening, non-judgement and non-directive talk. The participant will then view an online video clip involving a story from someone who has experienced this barrier, which is overlaid with an animation to make it especially engaging, and relevant to the ‘in-group’ targeted [30]. The intervention contains elements of ‘modelling’. Both video stories and quotes in the written material are generated from qualitative and public involvement work which underpinned the development of the intervention, with many of the video stories featuring members of a community advisory group.

While in the dental setting, using the booklet material, participants will make a goal regarding attending for a planned dental appointment, and an action plan that will help them overcome their chosen barrier to dental visiting. These will be photographed by the dental nurse on the Tablet PC and uploaded to the trial database to facilitate a follow-up text which will be sent within 2 weeks of the participant receiving the intervention. For participants who discuss more than one barrier within a delivery session, encouragement will be provided by the trained dental nurse to look at relevant intervention materials at home. Participants will receive a follow-up text with an online link to the material and videos which will be accessed via a restricted access web portal, and with a supportive message around the participant’s goal and action plan(s) recorded.

#### Criteria for discontinuing or modifying allocated interventions {11b}

Once patients are randomised to receive the intervention, there will be no modification of intervention content.

#### Strategies to improve adherence to interventions {11c}

A key component of the intervention is the conversation between the person delivering the intervention and the patient, which is to be conducted in a non-judgemental and supportive manner. All staff delivering the intervention will be trained according to a written intervention delivery manual. Training of staff will include both didactic teaching and role play, followed by a period of shadowing of intervention delivery (the member of staff first observes the intervention being delivered in situ, and then delivers it themselves while being observed by a member of the research team). An observation checklist containing essential elements of the intervention to be included is completed. This covers five essential domains: (i) empathetic listening with non-directive and non-judgement talk; (ii) elicitation and discussion of barriers to planned dental visiting leading to introduction of the booklet pack; (iii) being shown a video clip with patients’ reflection on how this relates to their own circumstance; (iv) highlighting relevant aspects of the booklet pack relevant to the patient’s circumstances, emphasising benefits of planned dental visits, hope for the future and assurance about the patients’ capability of overcoming relevant barriers; and (v) setting of a planned dental visiting goal and action plan relating to at least one barrier which is specific, measurable, achievable, realistic and anchored within a time frame (SMART). When the member of staff is observed to deliver at least 80% of these elements contained under each domain of the intervention in situ, they are deemed to be competent to deliver the intervention independently. In order to ensure consistency between raters of intervention delivery competency, a calibration exercise will take place using audio recordings of delivery sessions undertaken by RETURN research nurses, independent observation checklist scoring, comparison and group discussion. The exercise will be repeated until all discrepancies in scoring are resolved. A sign off guidance document will be produced to facilitate consistent sign off decisions.

In order to monitor fidelity of intervention delivery, all intervention delivery sessions will be audiotaped, with consent from both the patient and dental nurse. Recordings will be collected from research sites on a monthly basis throughout the recruitment period. Each month, 20% of the recordings from each dental nurse will be randomly selected and independently rated by two members of the research team using the observation checklist outlined above. Eighty percent of the necessary components will need to be present in each recording for the intervention delivery session to be deemed as reaching an acceptable fidelity threshold. If there is disagreement between the two raters, this will be resolved through discussion until agreement is reached. Where necessary, a third rater will be introduced to resolve disputes in scoring. In each instance where a recording is found to not have reached the fidelity threshold of 80%, feedback will be provided to the dental nurse in question using supervision sessions. Thereafter, a necessary refresher training and further shadowing will be undertaken if any member of staff delivering the intervention is found not to be delivering the key intervention ingredients consistently.

#### Relevant concomitant care permitted or prohibited during the trial {11d}

To avoid potentially confounding issues, co-enrolment in other dental trials is discouraged, although will be considered if viewed by the research team as not having a potential impact on the dental care or oral health of RETURN participants.

#### Provisions for post-trial care {30}

There are no anticipated harms from trial participation and therefore no arrangements for post-trial care.

### Outcomes {12}

#### Primary outcomes

Attendance at a dental practice for a planned care appointment within 12 months, collected from NHS Business Services Authority (BSA) data.Self-reported oral health-related quality of life as measured by the value at 12 months of the summary score of the short form Oral Health Impact Profile (OHIP-14) [33].

#### Secondary outcomes

Attendance at a dental practice for a planned care appointment, self-reported from phone calls at 6, 12 and 18 months.Attempt to make a planned care appointment, self-reported from phone calls at 6, 12 and 18 months.Attendance at a dental practice for a planned care appointment within 18 months, collected from BSA data.Self-reported oral health-related quality of life, measured by the final value at 6 and 18 months adjusting for the baseline value, of the summary score of OHIP-14 [33].Urgent attendance for dental care at dental practice, A&E or Dental Hospital. Patient self-reported at 6, 12 and 18 months.Halitosis and bad taste, measured by patient self-report at 6, 12 and 18 months.Treatment received, as measured by BSA clinical dataset, Dental Hospital audit and patient self-report at 6, 12 and 18 months.Antibiotic prescription by dentists, measured by BSA data, Dental Hospital audit and patient self-report at 6, 12 and 18 months.Antibiotic prescription by GP/A&E/Walk-in centre measured by patient self-report at 6, 12 and 18 months.Analgesic prescription, measured by patient self-report and Dental Hospital data at 6, 12 and 18 months.(safety): Dental anxiety, as measured by the change in the continuous score of the Modified Dental Anxiety Scale (MDAS) [32] recorded in patient self-report at 6, 12 and 18 months.Incremental cost-effectiveness ratio at 12 and 18 months derived from BSA data, patient self-report resource use and EQ-5D-5L at baseline, 6, 12 and 18 months.

Where an outcome measure (secondary outcomes 7, 8 and 10) using data from different sources produces conflicting results, e.g. NHS BSA and patient self-reports on treatment received, the outcome will be recorded as being present if recorded by either data source. Patient self-report of dental services used will include private as well as NHS services, whereas BSA data only records NHS services used.

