### Sample size {14}

Twenty six percent of patients attending urgent dental care access centres report they feel attending a dentist regularly is important [40] and other work shows that only 20% of users of such services have their own dentist [41]. Since unpublished data from an NHS evaluation in the North West of England found that an average of 16% of users of urgent dental care services delivered in dental practices returned to a practice for planned dental care over the subsequent 22 weeks, we estimated that over the longer period of 12 months, we might expect 30% of urgent dental care users to return for a planned dental care appointment. The calculation is based on a minimum clinically important difference of 10 percentage points (i.e. an improvement to 40% of patients attending a dentist) in the first of the joint primary outcomes. We estimate there is a possibility of some contamination between patients within practices. Rather than use a cluster randomised design, we have reduced the difference we want to detect to 9 percentage points to allow for potential contamination. Based on this, a sample size of 559 per group would give 80% power at *α* = 0.025 (to allow for joint primary outcomes) to detect this improvement in the intervention group. Allowing for 5% loss to follow-up gives a total target sample size of 590 per group.

For the second primary outcome, OHIP-14, we estimate a standard deviation of 11 points at 1-year follow-up. We also assume a higher rate of loss to follow-up of 20% for this outcome, as it will require successful telephone follow-up. Based on this, our total sample size of 1180 will give 80% power to detect a minimum clinically important difference of 2.25 points, with *α* = 0.025.

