### Assignment of interventions: blinding

#### Who will be blinded {17a}

RETURN is an open trial and as such investigators involved in the delivery of the intervention and participants in the trial are not blind to allocations. The statistical analysis plan will be written prior to the statistical team having access to any unblinded trial data.

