### Data collection and management

#### Plans for assessment and collection of outcomes {18a}

Table 1 provides a summary of procedures and assessments relative to participant timelines. Patients receiving dental care in an NHS dental practice following baseline will have a centrally held record in data held by NHS BSA, which will require participant IDs collected at baseline to be matched with participant NHS BSA identifiers. To maximise matching of participant descriptors with routinely held NHS BSA follow-up data, participant postcodes will be checked at each follow-up point in case this has changed since baseline. For participants receiving dental care in the Dental Hospital (DH) following their baseline data, details will be retrieved from clinical records held in the Dental Hospital identified by their unique RQ number. This follow-up data will be collected using a CRF proforma and conducted as an audit of participant DH records. Follow-up data collected by telephone calls by the central research team will be audiotaped and 10% checked by a different researcher than the researcher entering the data during the telephone call. Where disagreements are identified, these will be addressed and resolved by agreement, and any data entry errors rectified. Data collection forms can be obtained from the research team.

**Table 1 Tab1:** Schedule of processes and assessments

Procedures		Screening /Baseline	RETURN Intervention Group	Control Group	Follow-up		
					6 months (+/− 4 weeks)	12 months (+/− 4 weeks)	18 months (+/− 4 weeks)
Assessment of Eligibility Criteria		X					
Signed consent form		X					
Urgent dental treatment (trial processes and intervention around delivery of urgent care)		(X)	(X)	(X)			
Collection of Contact Details, including Home Postcode (to determine IMD as a mediator)		X					
Verification of NHS BSA Matching Descriptors					X^d^	X^d^	X^d^
Collection of RQ6 number^a^		X					
***Self-Reported Assessments***	Socio-economic status (Education level, employment and benefit status)	X			X^b^	X^b^	X^b^
	Age	X					
	Gender (including ‘prefer not to say’)	X					
	Ethnicity	X					
	OHIP-14	X			X	X	X
	Halitosis and Bad Taste	X			X	X	X
	EQ-5D-5L questionnaire	X			X	X	X
	Protection motivation theory questionnaire	X	X^c^	X^c^	X	X	
	Modified dental anxiety scale (MDAS)	X			X	X	X
	Use of Routine Dental Practices and Type (NHS or Private)	X			X	X	X
	Use of Student Teaching Pathway (Dental Hospitals)	X			X	X	X

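### Urgent dental attendance (secondary outcome 5) rests on unblinded self-report alone, although the trial already obtains records that could check its NHS practice and Dental Hospital parts

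*Protocol article*

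**What the plan says.** The protocol article (Secondary outcomes) defines the fifth secondary outcome as "Urgent attendance for dental care at dental practice, A&E or Dental Hospital. Patient self-reported at 6, 12 and 18 months". The matching entry under Secondary objectives is also self-report, but lists slightly different settings: "self-reported rates of attendance for urgent dental care at A&E, GP practices and urgent dental care services at 6, 12 and 18 months". Under Who will be blinded {17a}, "participants in the trial are not blind to allocations".

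Other sections describe records that cover part of the same ground. Plans for assessment and collection of outcomes {18a} states: "Patients receiving dental care in an NHS dental practice following baseline will have a centrally held record in data held by NHS BSA". The same section provides for an audit of Dental Hospital records for participants treated there after baseline. The BSA data run to 18 months, since another secondary outcome is "Attendance at a dental practice for a planned care appointment within 18 months, collected from BSA data".

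Neighbouring outcomes use these sources. Outcome 7 is "Treatment received, as measured by BSA clinical dataset, Dental Hospital audit and patient self-report at 6, 12 and 18 months", and outcome 8 (antibiotics prescribed by dentists) uses the same three sources. A rule that counts an event if either source shows it is given for outcomes 7, 8 and 10 only. The article also notes that BSA data hold NHS care only, whereas self-report includes private care.

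**The concern.** The Background argues that people without planned care fall back on repeated, costly urgent visits. Outcome 5 is the outcome that most directly shows whether the intervention changes this, so its measurement matters more than its place in the list suggests.

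Self-report is open to a difference between arms here. Only the intervention arm receives material on what it costs to wait for toothache, sets a goal for planned visiting, and gets a text that reinforces the goal. Such participants might mention fewer urgent visits, or describe an urgent visit as a planned one. Either would look like a benefit. For planned attendance, the self-reported result can be set beside the BSA result in each arm. For urgent attendance no such comparison is planned, although records for part of it will be in hand.

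**Working it through.** **1. Sources named for each outcome (Primary outcomes; Secondary outcomes).**

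| Outcome | Self-report | BSA | Dental Hospital records |
|---|---|---|---|
| Planned attendance | yes (secondary 1) | yes (first primary; secondary 3) | not named |
| Urgent attendance (5) | yes | no | no |
| Treatment received (7) | yes | yes | yes |
| Antibiotics from dentists (8) | yes | yes | yes |
| Analgesics (10) | yes | no | yes |

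Urgent attendance is the only one of these with no record-based component.

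**2. Could the records identify urgent visits?** The article does not say so outright. The first primary outcome requires planned care to be picked out in BSA data, so some classification of visits must exist. The sensitivity analysis in Statistical methods {20a}, which removes practice-recruited participants with no matched BSA record at baseline, suggests that the index urgent visit normally leaves a BSA record. Neither fact proves that every visit not classed as planned is urgent.

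**3. What the records cannot reach.** Private visits are outside BSA data, and no record source is described for A&E or GP visits. Self-report is still needed for these. Table 1 already lists self-reported use of GP and A&E services for urgent dental care at each follow-up.

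**4. The plan's own figures.** No rate or power is stated for urgent attendance. The Sample size {14} figures that depend on loss to follow-up can be reproduced:
- First primary outcome: 559 / (1 − 0.05) = 588.4, rounded up to 589 per group, against 590 stated.
- OHIP-14, for which the article says "We also assume a higher rate of loss to follow-up of 20% for this outcome, as it will require successful telephone follow-up": 1180 × 0.80 / 2 = 472 per arm. Then 2.25 / (11 × √(2/472)) − 2.241 = 3.142 − 2.241 = 0.901, which gives 81.6% power against 80% stated.

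**5. Illustration of reporting bias (assumed inputs).** Let p be the true rate of urgent attendance, equal in both arms, and d the shortfall in reporting completeness in the intervention arm. The spurious difference is p × d.
- Complete reporting in controls and p = 40%: with d = 0.10, 0.40 × 0.90 = 36%, a spurious 4 points; with d = 0.20, 0.40 × 0.80 = 32%, a spurious 8 points.

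For the chance of a false significant result, assume 90% reporting in controls, 472 per arm and a two-sided 5% test. With reported rates p₁ = 0.9p and p₂ = (0.9 − d)p, the probability is Φ((p₁ − p₂ − 1.96 × SE₀)/SE₁) plus a negligible opposite tail. SE₀ uses the pooled rate and SE₁ the separate rates. For p = 40% and d = 0.10, p₁ = 0.36, p₂ = 0.32, SE₀ = 0.0308 and SE₁ = 0.0308, so Φ((0.04 − 0.0604)/0.0308) = Φ(−0.66) ≈ 25%.

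| True rate p | d = 0.05 | d = 0.10 | d = 0.20 |
|---|---|---|---|
| 20% | 1.0 points, 7% | 2.0 points, 13% | 4.0 points, 39% |
| 30% | 1.5 points, 8% | 3.0 points, 18% | 6.0 points, 58% |
| 40% | 2.0 points, 10% | 4.0 points, 25% | 8.0 points, 75% |
| 50% | 2.5 points, 12% | 5.0 points, 34% | 10.0 points, 88% |

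Each cell gives the spurious difference and the false-positive rate at a nominal 5%.

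**The case against.** **Self-report is the only source that spans every setting.** The outcome covers A&E, its objective adds GP practices, and private care is outside BSA data. Outcome and objective agree on self-report, so this is no contradiction. All of this stands. It is a reason to keep self-report, but not a reason to leave the NHS practice and Dental Hospital parts unchecked.

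**Indirect checks exist.** A reader might infer that the trial could never tell a real fall in urgent visits from a reporting difference. That goes too far. Planned attendance is collected both by self-report and from BSA data, so relabelling of visits as planned could be looked for by arm. Outcomes 7 and 8 also draw on records of related care. But no such comparison is stated, and none measures urgent attendance itself. The 10% check of recorded calls addresses data entry, not recall.

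**The bias is hypothetical.** The article gives no urgent-attendance rate and no evidence of under-reporting, and it describes the intervention conversation as non-judgemental. This stands: the tables show sensitivity to assumptions and are not estimates.

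**Power.** A reader might infer that records would raise the numbers analysed from 944 (1180 × 0.80) to 1121 (1180 × 0.95) and so improve power. The article does not support this. The 20% and 5% are sample-size allowances for the two primary outcomes, and the 5% is not a stated BSA match rate. A record-only outcome omits A&E, GP and private visits, so its event rate would differ. A composite of records and self-report would still depend on telephone follow-up.

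**Recall period.** Six-month recall of visits is inferred from the spacing of contacts; Table 1 states that window only for prescriptions.

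**Conclusion.** The concern holds as a weak choice of measurement for one secondary outcome. Urgent attendance is fixed as self-report from unblinded participants, it alone lacks a record-based component among the outcomes compared above, and the relevant extracts are already being obtained. Differential under-reporting or relabelling in the intervention arm therefore could not be checked directly.

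Its size cannot be taken from the article. At an assumed equal true rate of 40%, a one-sided reporting shortfall of 10 to 20% would create a false reduction of 4 to 8 points. Smaller rates or shortfalls give less, and equal under-reporting in both arms would create no false difference where the true rates are equal. How far records can help depends on whether BSA data identify urgent care, which is implied but not stated. The primary outcomes and the sample size are unaffected.

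**What to change.** Add a record-based analysis of urgent attendance at NHS dental practices (BSA data) and the Dental Hospital (audit) at 6, 12 and 18 months. Exclude the index visit, and state how urgent care is identified in the BSA data and what is done if it cannot be separated from other non-planned care. Report it by arm alongside the self-reported outcome.

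Keep self-report for A&E, GP and private visits. Align the settings in outcome 5 with its objective, which lists GP practices; Table 1 already collects these visits.

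An either-source composite, as for outcomes 7, 8 and 10, may be added. It should not stand in for the record-only analysis, because it still carries self-report bias.

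The cost is outcome wording and one derivation from data already obtained. The limits are that records miss private, A&E and GP care, and that participants not matched in BSA data may be wrongly counted as having no urgent visit. The sensitivity analysis already planned for unmatched participants in the first primary outcome could be repeated here.
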